#### E-cigarettes with counselling

To determine the effects of e-cigarettes and smoking cessation in pregnant women, Chiang et al. [13] conducted a two-arm RCT. The first group received cigarettes and text messages, while the other group received e-cigarette with dual use of cigarettes and text messages. The eligibility age was 14 years or older, currently pregnant, possesses a smartphone, willingness to receive texts, and smoked at least 15 cigarettes in the past 2 weeks. The impact of e-cigarettes on CPD was the primary outcome. Smoking cessation at the 7-day period of abstinence was the secondary outcome. The effect of e-cigarettes was investigated with the simple mean difference values. The results of this pilot study with 471 participants showed that e-cigarette’s impact on smoking behaviors among pregnant women in the USA is mixed, and relative effect of e-cigarettes on smoking reduction should be examined in future.

A study by Nancy et al. [14] examined the relationship between e-cigarette use and smokers quitting smoking after a hospitalization. One of the groups received regular standard care, whereas the other received regular care plus an intervention. The main result was the use of e-cigarettes in the first 3 months following discharge, with tobacco abstinence measured at 6 months using biochemically validated measures. To calculate the intervention impact of abstinence, propensity score matching (PSM) approaches were employed. The analysis of 1100 participants revealed interesting facts. Over 25% of smokers who were trying to quit used e-cigarettes for 3 months. When compared to smokers who did not use e-cigarettes regularly, this pattern of e-cigarette usage was related with a lower 6-month rate of tobacco abstinence. Further research is necessary to determine whether routine use of e-cigarettes promotes or inhibits smoking cessation.

The study by Halpern et al. [15] looked at e-cigarettes, rewards, and medications for cessation with a pragmatic trial. Usual care, free e-cigarettes, an incentive plus free cessation aids, and a redeemable deposit plus free cessation aids were the five implemented interventions. The biochemical proof of urine sample with a cotinine level of less than 20 ng per milliliter was the main technique for verifying abstinence. The impact of the interventions was determined by using the logistic regression analysis. Financial incentives increased the rate of maintained smoking cessation compared to free cessation aids. To better understand the short-term effects of e-cigarettes with high smoking-related risk, Masiero et al. [52] opted for ca double-blind, three-arm RCT with standard care, e-cigarettes, and standard care, as well as a placebo e-cigarette. The eligibility requirements included at least 55 years old, smoking an average of 10 CPD or more for at least in the last 10 years, and not being engaged in any other quit program.

The primary objective was a change in pulmonary function (dry cough, shortness of breath, mouth irritation), while the secondary outcomes were a change in daily cigarette consumption and a change in the carbon monoxide concentration of expired air. Group comparisons were made based on nonparametric statistics. To analyze differences in respiratory symptoms, e-cigarette side effects, and any other categorical factors, a chi-square test was specially applied. To assess statistical differences in cigarettes, the Mann-Whitney *U*- (for two samples) and Kruskal-Wallis *H*- (for three samples) tests were utilized. The findings showed that e-cigarettes helped participants quite smoking and reduced CPD rate significantly decreased compared to the baseline values. This was valid for smokers who were prepared to stop smoking, but it can also be helpful for less motivated smokers taking part in clinical settings.

To test the efficacy of counselling, e-cigarettes plus counselling, and non-nicotine e-cigarettes plus counselling on smoking cessation, Eisenberg et al. (2020) [53] conducted three arms with a multicenter RCT. Adults who wanted to stop smoking and averaged at least 10 CPD were eligible. The point prevalence smoking abstinence was at 12 weeks after randomization, and the 7-day secondary end point was at 24 weeks, which were assessed at various follow-ups. Based on the binomial distribution, the pairwise comparison and risk differences with 95% confidence level were estimated. With logistic regression models, odds ratios were estimated. The analysis of data from 376 participants showed that for smokers motivated to quit smoking, the use of nicotine e-cigarettes in combination with counselling, opposed to counselling alone, significantly boosted point prevalence abstinence at 12 weeks. The differences were no longer significant at 24 weeks.

Martinez et al. [16] conducted a three-arm RCT to examine smoking cessation among dual users of combustible cigarettes and e-cigarettes. The first group received self-help booklets, while the second group received smoking cessation self-help booklets and monthly cessation materials, and the third group received dual user-specific booklets and monthly cessation materials. The eligibility requirements included at least 18 years old, smoking once a week or more in the prior year, and vaping once a week or more in the previous month. Across America, participants were enrolled using print, electronic, and social media forums. Self-reported 7-day point-prevalence smoking abstinence at each assessment point served as the primary outcome. Secondary outcomes were 7-day point-prevalence vaping abstinence and the cost per incremental smoking cessation. Generalized estimating equations and mixed analysis with univariate and multivariate logistic regression evaluated the effectiveness of interventions. Findings from a total of 2896 participants show that self-help information with e-cigarettes has a large potential for encouraging smoking cessation for those who use both combustible cigarettes and e-cigarettes.

#### E-cigarettes and NRT with nicotine and non-nicotine

Using a three-arm study design, Caponnetto et al. [17] conducted a 12-month randomized controlled trial to evaluate the effectiveness of e-cigarettes as a combustible smoking substitute. The study included e-cigarettes without nicotine, with 7.2 mg of nicotine, 5.4 mg of nicotine for the first two quarters, and 7.5 mg for the second two quarters. The eligibility requirements included being between the ages of 18 and 70, having smoked 10 cigarettes per day for the preceding 5 years, being in excellent health, and not actively trying to quit smoking or planning to in the next 30 days. The abstinence was examined with the carbon monoxide test. The main result was a 7-ppm CO concentration without smoking. For group comparison, nonparametric econometric tests were applied. There were 3 follow-up intervals: 12, 24, and 52 weeks. The findings support the claim that using e-cigarettes, both with and without nicotine, dramatically reduces the consumption of conventional cigarettes and results in long-lasting tobacco abstinence without having any negative side effects.

Tseng et al. [17] carried out a randomized control trial comparing the nicotine-containing electronic cigarettes with a placebo in terms of smoking cessation in young adults. The double-blind two-arm RCT had 99 subjects who were current smokers with greater than 10 CPD and validated greater than and equal to 8 ppm. The eligible age range was 21 to 35. The main result was a self-reported decrease in CPDs of more than 50% participants after three weekends of treatment. Multiple logistic regression analysis investigated the contribution of the predictors to the result of smoking reduction and repeated measure. ANOVA statistics examined variation within and between CPD rates. With the use of e-cigarettes, a diverse young adult sample of current, daily smokers who were not ready to quit were able to cut back on smoking. To determine the function of nicotine- and placebo-containing e-cigarettes in promoting reduction and subsequent cessation, more research is required.

With a double-blind three-arm study, Backer et al. [54] investigated the role of NRT in conjunction with low nicotine cigarettes for smoking cessation. The participants were smokers who had smoked an average of 15 cigarettes per day for at least 1 year before randomization and were between the ages of 21 and 65 years. Entry into the study required a carbon monoxide (CO) measurement of 15 ppm. The primary endpoint was 4 weeks of abstinence, which was established by self-report and verified by inhaled CO < 10 ppm for each individual, and continuous abstinence recorded from weeks 7 to 10. The intent-to-treat (ITT) and Fisher exact test evaluated hypotheses. To identify prognostic markers and conduct an adjusted analysis of the primary outcome, logistic regression was used. At the analysis level, 346 samples were obtained, including 114 for control and 232 for treatment groups. According to the trial findings, Quest brand of cigarettes plus NRT was more effective than active control plus NRT in attaining 4 weeks of continuous abstinence. There were no major side events associated with the investigational product. Walker et al. [55] assessed the combined effect of low nicotine cigarettes, NRT, and behavioral quit line care in a single-blind two-arm research. The participants were 18-year-old smokers interested in quitting smoking. The participants were not eligible if they were pregnant/breastfeeding, presently using NRT or non-cigarette tobacco products, had a stroke or angina in the previous 2 weeks, or were taking bupropion, clonidine, or other similar medications.

The primary outcome was smoking abstinence for 7 days, and the quit data was after 6 months. To analyze the treatment effect over time, repeated-measures analyses were also performed with generalized estimating equation (GEE) models. According to the findings, some smokers may be helped to quit by adding low nicotine cigarettes to the normal Quitline smoking cessation support.

By using a randomized control trial, Janet et al. [18] studied how to improve quit-and-win competitions to increase cessation among college smokers. The study had two groups: one with 615 participants in a multiple contest with no counselling and 602 individuals in a single contest with counselling. The minimum age to participate was 18. At the completion of the treatment, the 30-day point prevalence-verified abstinence after 6 months was the primary outcome. The secondary outcome was the same at 4 months. To determine how treatments affect the prevalence of smoking, the logistic and generalized linear mixed models were used. After a 6-month follow-up, analysis showed multiple contests with college students were a more suitable and effective strategy to raise the rate of smoking abstinence than a single contest, while there were no strong signals regarding the counselling.

## Materials and methods

### Data

#### Study population

The adult smokers who are at least 18 years reside in Pakistan and smoke cigarettes daily. Additionally, they are ready to meet the inclusion requirements and motivated to establish a quit date within the next 2 weeks of recruiting. Note that other nicotine- and non-nicotine-based cessation therapies will not be allowed during the trial.

#### Inclusion criteria

The potential participants for the trial will have to meet the following requirements.◦ Participants are at least 18 years old. Upper age limit is 65 years.◦ Smoke more than 10 combustible cigarettes a day at the time of study enrollment◦ Smoking cigarettes for at least a year◦ Participants are willing to stop combustible smoking.◦ Participants are ready to sign a written consent form.◦ There can only be one applicant per household.◦ Own a phone that supports text messaging

#### Exclusion criteria

The potential participants will be not considered in case they are the following:Women who are pregnantCurrently using other nicotine- and non-nicotine-based cessation therapiesFemales who intend to become pregnant during the trial’s participation termExperiencing chest pain or another cardiovascular event or procedure (e.g., heart attack, stroke, insertion of stent, bypass surgery).

#### Sampling strategy and sample selection

Keeping in view the study objectives, the process of deciding the number of observations/sample respondents would be made through the determination of sample size, which is based on the extent and intensity of variation and heterogeneity in the subject population. For a population with lower variation, a small sample is adequate and vice versa, ceteris paribus. In empirical studies aimed at representing the salient features of the population under study, the sample size is important. Before calculating the sample size, a few details about the target population, including its size, variance, margin of error, and desired level of confidence in empirical estimates of important variables, are required [56]. A major constraint in arriving at the ideal sample size is the lack of adequate information and data regarding the standard deviation of variables/indicators. In the absence of this specific information, this study referenced international studies conducted in a similar design, although some variations were noted. To prevent bias, the study opted for the most suitable sampling method considering the budget constraints and local limitations related to variations in the target population. The study employed the equivalence trial formula to estimate the primary outcome, which focused on reducing the use of combustible cigarettes through the provided interventions (Table 1).$${n}_1={\left({Z}_{1-\frac{\alpha }{2}}+{Z}_{1-\beta}\right)}^2\ \frac{p_1\left(1-{p}_1\right)+{p}_2\left(1-{p}_2\right)}{{\left({p}_1-{p}_2\right)}^2}$$where$${p}_1= Proportion\ of\ outcome\ from\ group-1$$$${p}_2= Proportion\ of\ outcome\ from\ group-2$$$$\alpha = Level\ of\ significance$$$$1-\beta = Power\ of\ test$$$${Z}_{1-\alpha /2}=Z\ value\ of\ corresponding\ level\ of\ significance$$$${Z}_{1-\beta }=Z\ value\ of\ corresponding\ level\ of\ power$$$${n}_1= Sample\ size\ for\ one\ group$$

**Table 1 Tab1:** Sample size calculation based on previous studies

Indicators	Information	Study: Hajek et al. (2019) [50]	Study: Smith et al. (2022) [12]	Study: Rigotti et al. (2018) [14]	Study: Caponnetto et al. (2013) [16]
	Rounded figures				
Proportion of outcome from group 1 (p1)	0.18	18%	26%	10%	14%
Proportion of outcome from group 2 (P2)	0.09	9%	6%	26%	5%
Level of significance (alpha)	0.05				
Power (1-beta)	0.8				
Z alpha	1.96				
Z beta	0.84				
Sample size group 1 (n1)	222.1	222	49	86	163

Based on the aforementioned formulas, from Hajek et al. [50], Smith et al. [12], Rigotti et al. [14], and Caponnetto et al. [16] derived 222, 49, 86, and 163 for single group respectively. According to acceptable norms and standards, the selected sample should represent the population. By the safe decision and following the abovementioned procedure, this study proposes a sample size of 600 participants, which will be randomly divided into three groups as follows:E-cigarette: The 200 participants will receive e-cigarettes along with basic care counselling.Nicotine pouches: The 200 participants will receive nicotine pouches along with basic care counselling.Basic care counselling: The 200 participants will receive basic care counselling.

Under the Lead Researcher [name], ARI team will conduct interview of participants and assign and unique ID to each potential participant at the screening stage. After that, the lead research Dr. [name] will generate the allocation sequence and will assign participants to interventions by using STATA software for the randomization.

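### The 86 per group in Table 1 comes from a comparison in which e-cigarette use went with less quitting, and no column establishes 80% power against counselling alone

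*Protocol article*

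**What the plan says.** Under Sampling strategy and sample selection, Table 1 puts pairs of outcome proportions into a two-proportion formula with "Level of significance (alpha) 0.05" and "Power (1-beta) 0.8". A working column uses 0.18 versus 0.09. Four source columns use 18% versus 9% (reference 50), 26% versus 6% (reference 12), 10% versus 26% (reference 14) and 14% versus 5% (labelled reference 16). The text after the table reports that these "derived 222, 49, 86, and 163 for single group respectively" and continues: "By the safe decision and following the abovementioned procedure, this study proposes a sample size of 600 participants", split into three arms of 200: e-cigarettes plus counselling, nicotine pouches plus counselling, and counselling alone. The abstract says that this total is enough to assess both products.

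The literature review describes the sources. Of reference 14 it says that propensity score matching was used and that "this pattern of e-cigarette usage was related with a lower 6-month rate of tobacco abstinence". Of the nicotine versus nicotine-free e-cigarette trial it says that participants were "not actively trying to quit smoking or planning to in the next 30 days".

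**The concern.** The formula squares p1 − p2, so it gives the same sample size whether group 1 does better or worse. Reference 14 is the only column with p1 below p2, and the review reports an adverse association for it. Its 86 is nevertheless listed beside the other three sizes without comment.

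Beyond that column, a sample size supports a trial only if its rates belong to the contrast that the trial will test. Here that is a product plus counselling against counselling alone, in smokers motivated to set a quit date. If no column describes that contrast, the 80% in Table 1 belongs to other comparisons. A null result for either product could then be read as coming from an adequately powered trial when the protocol has not shown this.

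**Working it through.** **1. Reproduce the plan's figures.** The formula in the sample-size section is n = (1.96 + 0.84)² × [p1(1 − p1) + p2(1 − p2)] / (p1 − p2)², with (1.96 + 0.84)² = 7.84.

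| Source column | p1, p2 | Calculation | n | Printed |
|---|---|---|---|---|
| Ref. 50 (and working column) | 18%, 9% | 7.84 × 0.2295 / 0.0081 | 222.1 | 222 |
| Ref. 12 | 26%, 6% | 7.84 × 0.2488 / 0.0400 | 48.8 | 49 |
| Ref. 14 | 10%, 26% | 7.84 × 0.2824 / 0.0256 | 86.5 | 86 |
| Fourth source | 14%, 5% | 7.84 × 0.1679 / 0.0081 | 162.5 | 163 |

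All four reproduce. Swapping 10% and 26% leaves 86.5 unchanged, so the size alone does not reveal the direction.

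**2. Set each source beside this trial's contrast**, using the protocol's own literature review.

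- Ref. 50 and ref. 12: e-cigarettes versus NRT. This trial has no NRT arm.
- Ref. 14: users versus non-users of e-cigarettes after hospitalisation, analysed with propensity scores, with lower abstinence among users. Table 1 does not say which group is p1, but the reversed order fits users at 10%.
- Fourth source: e-cigarettes with and without nicotine, in smokers not trying to quit. This trial enrols smokers motivated to set a quit date within 2 weeks. (Table 1 labels the source reference 16, while the matching description in the review carries reference 17. Neither description is of a product plus counselling versus counselling alone.)
- Nicotine pouches: in no column.

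The review does describe one trial of e-cigarettes plus counselling versus counselling alone, in motivated smokers, but gives no abstinence rates for it. No corrected sample size can therefore be computed from the protocol.

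**3. Does removing the 86 change the total?** No. The remaining sizes are 222, 49 and 163, and the largest is still 222.

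**4. Power at the planned 200 per arm.** Power = Φ{|p1 − p2| / √([p1(1 − p1) + p2(1 − p2)]/200) − 1.96}.

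At the working rates: √(0.2295/200) = 0.03388; 0.09/0.03388 = 2.657; 2.657 − 1.96 = 0.697; power = 75.7% (75.2% with a pooled variance). At 222 per arm the same formula gives 79.9%.

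**5. Sensitivity to the unstated counselling-alone rate**, with the product held at 18%:

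| Counselling alone | Power at 200 per arm |
|---|---|
| 6% | 96.4% |
| 9% | 75.7% |
| 10% | 64.1% |
| 12% | 39.2% |

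The 18%, 9% and 6% appear in Table 1, though not as rates for these arms. The 10% and 12% are assumptions chosen to show the range.

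**The case against.** The strongest reply is that nothing printed is miscalculated and that the 86 is harmless. The working column is 18% versus 9%, and deleting reference 14 leaves the largest requirement where it was. That stands: the 86 does not drive the total.

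Second, the protocol concedes that specific information was lacking and that its source studies varied in design. Borrowing from imperfect comparators is common. This stands in part. The disclosure is general, and it does not tell the reader that one source points the other way or that none has this trial's control.

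Third, parts of the reading of reference 14 are inferred. Table 1 does not label its groups, and the Introduction lists that study among randomised trials. The e-cigarette comparison that the review describes is nevertheless one of use, not of assignment.

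Fourth, the Retention section promises to enrol above the optimum size. It gives no number, and the design still randomises 600, whereas 3 × 222 = 666.

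Some stronger inferences are tempting but unsupported:

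- A reader might conclude that the trial is underpowered against counselling alone. The effect there could be larger or smaller than against NRT.
- A reader might take the counselling-controlled trial as evidence of a smaller effect, because "The differences were no longer significant at 24 weeks". That trial had 376 participants over three arms, and non-significance without rates says little about effect size.
- A reader might suppose that 200 was called safe because three of the four sizes lie below it. The text gives no such reason.
- A reader might compute near-zero power to show benefit under 10% versus 26%. The plan never assumes that truth, so the figure says nothing about this trial.

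**Conclusion.** The point holds as one of justification, not of calculation. The 86 should not be offered as support, because the review reports its source as an adverse association by use of e-cigarettes. Reading the 10% as the users' rate is an inference, but the one that fits both the text and the column order. The remaining columns concern other controls, one of them also another population, and none concerns pouches. Table 1 therefore leaves 80% power unestablished for both comparisons with counselling alone, without showing that it is absent.

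One shortfall does follow from the plan's own figures: at 18% versus 9%, 200 per arm gives about 76% power. This assumes two-sided alpha 0.05, the unpooled normal approximation, no dropout and no adjustment for having two products. Beyond that, power depends strongly on a counselling-alone rate that the protocol never states, running from 96% to 39% as that rate moves from 6% to 12% with the product at 18%.

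**What to change.** In Table 1 and the paragraph after it:

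1. Delete the 10% versus 26% column, and the 86 as support.
2. Define p1 as the rate with product plus counselling and p2 as the rate with counselling alone.
3. State that the borrowed rates are assumptions taken from other comparisons, and that the pouch rate has no source.
4. Keep 200 per arm and replace the single 80% with the power at that size: about 76% for 18% versus 9%, with the range over assumed counselling-alone rates (product at 18%: 96% at 6%, 64% at 10%, 39% at 12%). Give the same range for pouches, labelled as an assumption.
5. Reword the abstract's claim that 600 is enough so that it matches.

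The cost is rewording one table, one paragraph and one sentence of the abstract, with no added participants. The downside is a power statement that is conditional and less favourable.

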#### E-cigarettes with NRT intervention

A randomized trial of e-cigarettes for quitting smoking conducted by a study [49] used a three-arm design — e-cigarettes with nicotine, nicotine patches, and placebo e-cigarettes. The criteria for eligibility included at least 18 years old, smoking 10 or more cigarettes per day (CPD) for the previous year, wanting to quit, and being able to give consent. The main result was quitting smoking for seven days. The follow-up periods were 1, 3, and 6 months. The treatment and the control groups were compared with multivariate regression adjustment and the *χ*^2^ test. According to the findings, e-cigarettes, whether they included nicotine or not, were only slightly more efficient than nicotine patches at aiding smokers in quitting. A few negative side effects were also noticed. E-cigarettes’ role in tobacco control was found to be unclear, with additional research recommended to clarify their overall advantages and disadvantages, both for individuals and for populations.

To determine the effectiveness of e-cigarettes and NRT for smoking cessation, another study [50] conducted a two-group pragmatics multicenter RCTs. The first group received nicotine replacement treatment, while the second group was given cigarettes. To examine the effects of e-cigarettes and NRT, a total of 884 subjects were analyzed using follow-up technique. The primary objective was sustained abstinence for 1 year. It was confirmed biochemically and assessed using a mixed-method analysis with binary regression and the generalized linear method (GLM), while secondary outcomes included participant-reported treatment use and respiratory symptoms. E-cigarettes were found to be more effective method of quitting smoking compared to NRT. Lee et al. [10] conducted a two-arm, single-center RCT to examine the efficacy of e-cigarettes and NRT for smoking reduction and cessation. Male adults over 18 who had smoked for at least 3 years and who were motivated to quit smoking altogether or cut back on their cigarette intake were qualified as eligible subjects if they had smoked at least 10 CPD in the year prior.

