#### Primary outcomes

The primary outcome will be long-term change in health status. The best proxy indication for demonstrating a reduction in toxin intake from tobacco smoking that is adequate to result in a clinically relevant long-term health benefit is unknown [59]. In the absence of more accurate health indicators, the change in smoking rate from baseline and the smoking cessation will be the primary outcomes. This study will evaluate the impact of e-cigarettes and nicotine pouches on cigarettes per day (CPD and smoking cessation (7-day point abstinence) at weeks 24 and 48 (the study period ends in 60 weeks. At 48 weeks, ARI will be ending the provision of the interventions). Self-reported point-prevalence abstinence in the previous week with biochemical validation will be exhaled carbon monoxide less than 10 parts per million (PPM).

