#### Data collection plan: retention

This study will enroll only the potential candidates who will continue until the end of the trial. Additionally, this study will also enroll a higher number of participants than the optimum sample size to mitigate sample bias.

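### Table 1 requires 222 per group for 18% vs 9% at 80% power, but 200 per arm is adopted without a reason; power is then about 76%, and the over-enrolment statement conflicts with 600

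*Protocol article*

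**What the plan says.** All references are to the protocol article.

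- **Sampling strategy and sample selection, Table 1.** The column headed as the planning information has "Proportion of outcome from group 1 (p1) 0.18", a second proportion of 0.09, "Level of significance (alpha) 0.05", "Power (1-beta) 0.8", and Z values of 1.96 and 0.84. Its result is 222.1 for one group. The 18% and 9% are those of the first of the four reference studies. Across the four, the text reports that the formula "derived 222, 49, 86, and 163 for single group respectively".
- **Same section, next paragraph.** "this study proposes a sample size of 600 participants, which will be randomly divided into three groups", with 200 in each of the e-cigarette, nicotine pouch and counselling-only arms. The number is presented as a safe decision that follows the procedure just described.
- **Abstract (Method) and Study design.** Both repeat 600 in total and 200 per arm. The Abstract calls this sufficient, and Study design gives 600 as the number randomised.
- **Data collection plan: retention.** "this study will also enroll a higher number of participants than the optimum sample size to mitigate sample bias". No number and no expected loss rate are given.
- **Outcome behind the planning rates.** The literature review (E-cigarettes with NRT intervention) says of the 18%/9% study: "The primary objective was sustained abstinence for 1 year". For this trial, Primary outcomes names cigarettes per day and "smoking cessation (7-day point abstinence) at weeks 24 and 48".

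**The concern.** The calculation and the chosen number are printed side by side and disagree. None of the four results is 200, their mean is 130, and a cautious choice among them would meet the largest, 222. The section mentions budget constraints when it explains the choice of sampling method, but it does not link them to the step from 222 to 200 and does not restate the power.

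A reader who meets 80% in Table 1 and is told that 600 is sufficient will take 80% as the design power. A null cessation result would then be read against a power that 200 per arm does not reach under the planning rates. The retention statement adds to this. It suggests a margin for loss over 60 weeks, while the only totals given leave none relative to 222 per group.

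**Working it through.** **Inputs (Table 1).** p1 = 0.18, p2 = 0.09, Z for two-sided 5% = 1.96, Z for 80% power = 0.84.

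**1. Reproducing the plan's figures.** The printed formula is n = (1.96 + 0.84)² × [p1(1 − p1) + p2(1 − p2)] / (p1 − p2)².

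- Variance sum: 0.18 × 0.82 + 0.09 × 0.91 = 0.1476 + 0.0819 = 0.2295.
- n = 7.84 × 0.2295 / 0.0081 = 222.13, against a stated 222.1.
- The other columns give 48.8 (26% vs 6%, stated 49), 86.5 (10% vs 26%, stated 86) and 162.5 (14% vs 5%, stated 163).

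All four reproduce.

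**2. Could another method give 200?** For 18% vs 9%, the pooled-variance version gives 226, and 247 with continuity correction. One-sided versions give 175 to 178, but the plan fixes Z at 1 − α/2, that is 1.96. No two-sided version gives 200.

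**3. Shortfall.** 222 − 200 = 22 per arm, and 22/222 = 9.9%. In total 3 × 222 = 666, or 669 if 222.13 is rounded up to 223. That is 66 to 69 more than 600.

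**4. Power at 200 per arm, 18% vs 9%.**

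- Unpooled, matching the plan's formula: Φ(0.09 / √(0.2295/200) − 1.96) = Φ(2.657 − 1.96) = Φ(0.697) = 75.7%.
- Pooled: the mean proportion is 0.135 and 2 × 0.135 × 0.865 = 0.23355. Φ((0.09 × √200 − 1.96 × √0.23355) / √0.2295) = Φ(0.680) = 75.2%.
- For comparison, 222 per arm gives 79.9% unpooled.
- Solving the unpooled expression for p1 with p2 = 0.09 and 80% power at 200 per arm gives p1 = 0.186.

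**5. Power at 200 per arm in the other scenarios (unpooled).**

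| Scenario | Power |
|---|---|
| 14% vs 5% | 87.4% |
| 10% vs 26% | 98.9% |
| 26% vs 6% | above 99.9% |

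**6. Attrition.** The article states no rate, so these losses are assumptions. Those lost are taken to contribute no outcome, and the rates stay at 18% and 9%.

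| Assumed loss | Analysed per arm | Power (unpooled) | Enrolment per arm to keep 222 |
|---|---|---|---|
| 10% | 180 | 71.2% | 247 |
| 20% | 160 | 66.1% | 278 |
| 30% | 140 | 60.4% | 318 |

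**The case against.** The strongest reply is that the plan nowhere claims 80% power for 600 participants. The 0.8 is an input to the 222 calculation, and 222 is printed openly near 200. The four scenarios are not formally ranked, 200 exceeds three of the four results, and raising 18% to 18.6% restores 80%, a shift well inside the uncertainty of rates borrowed from abroad. The calculation also says nothing about cigarettes per day, the other primary outcome. All of this stands, and it limits the seriousness. It does not remove the inconsistency: 18% vs 9% fills the only column that carries alpha, power and Z values, it gives the largest result, and 200 is said to follow from that procedure.

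A reader might infer more than the article supports:

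- **That the over-enrolment does not exist.** The retention section states an intention without a number, so enrolment beyond 600 cannot be excluded. It conflicts with the stated totals if 222 per group is the optimum, and agrees with them only against the three smaller results.
- **That the change of endpoint leaves the trial badly underpowered.** The mismatch is real, but its effect depends on what is assumed. At 200 per arm, 27% vs 18% (same gap) gives about 58% power, while 27% vs 13.5% (same ratio) gives about 93%. The section also concedes that the reference studies differ in some respects.
- **That two product comparisons must each be tested at 0.025.** The article sets no such rule.
- **That the 10%/26% column is reversed evidence.** Table 1 does not say which group is which. The literature review reports lower abstinence with e-cigarette use in that study but gives no abstinence rates, so what 26% represents cannot be settled from the article.

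**Conclusion.** The point holds. The sample-size calculation is correct, but the number adopted does not follow from it. At 200 per arm, power for 18% vs 9% at two-sided 5% is about 76%, some 4 points below the planning value, before any loss. This rests only on figures in Table 1; the attrition figures rest on assumed rates. The over-enrolment statement and the total of 600 cannot both stand against 222 per group as the optimum. The shortfall applies to one of four scenarios and affects no estimate or error rate, so this is a modest correction to a stated design figure and does not show that the trial is inadequate.

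**What to change.** Keep 600 and correct the text.

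1. In Sampling strategy and sample selection, state that 200 per arm gives about 76% power for 18% vs 9% at two-sided 5%, and that 80% power corresponds to about 18.6% vs 9%. Give the reason for going below 222. If the sponsor prefers to plan on 14% vs 5%, the section should say so and justify it.
2. Add power under assumed losses as a range: about 71%, 66% and 60% for 10%, 20% and 30%, labelled as assumptions.
3. Reconcile Data collection plan: retention with 600, either by giving the number actually to be enrolled (consistently in the Abstract and Study design) or by removing the statement.
4. State that 18% and 9% are one-year sustained-abstinence rates from a trial of e-cigarettes against nicotine replacement therapy, whereas this trial measures 7-day point prevalence against counselling alone.

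The cost is a text change and a less favourable stated power. Raising enrolment to 222 or 223 per arm (666 to 669 in total) plus an attrition allowance would also resolve the power shortfall, at the cost of at least 66 more participants.
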